### Safety and serious adverse events

The following are examples of potential adverse reactions: hyperkalemia, gastrointestinal dysfunction, immune system dysfunction, insomnia, serum glucose disruption, pruritus, pitting edema of the feet or legs, and abnormalities in serum transaminase and phosphocreatine kinase. To make it easier for patients to record accurately the shifts in their illnesses that occurred as a result of drug usage, the doctors will avoid asking patients leading questions. In addition to the therapeutic outcomes, any adverse events or unforeseen adverse reactions (signs, symptoms, and lab tests) will be noted. If there is a serious adverse event that takes place, the researchers will quickly implement the necessary treatment procedures. The drug will be withdrawn. The time of drug withdrawal, time of onset, length of symptoms, response to therapy, and the final result will all be documented. Within 24 h, the researchers will notify the ethics committee, the Drug Supervision and Administration Department, and any other applicable administrative agencies of any serious adverse events. The report will be signed and dated by the researchers.

### Data monitoring body and management

This research will be carried out in compliance with the guidelines for good clinical practice as well as the principles outlined in the Declaration of Helsinki. An independent clinical trial data management committee (CTDMC) composed of members of the ethics committee, neurosurgeons, physicians, information specialists, and intensivists will complete non-blinded evaluations of all of the patients’ effectiveness and safety data independently, comprising AEs and dropout rates, recorded from the time of informed consent to 180 days after the randomization process. The CTDMC is responsible for the examination and analysis of clinical data and holds regular meetings to control the quality of the trials.

The patient’s health records will be digitized and stored on a computer, and the data will be uploaded to the Electronic Data Capture system (ResMan, www.medresman.org). Details provided on the case data form will be checked for accuracy. Any changes or corrections made will retain a clear record of the original. When an amendment or correction is made, the researcher will note the date, sign their name, and provide an explanation (if required). All of the patient’s medical history, including any alterations, deletions, or updates, will be stored digitally. The audit trail will be secured in a way that prevents any unauthorized changes or deletions. The clinical data management system will have authority management such that only authorized personnel will be allowed to operate it. Electronic signatures are widely used in ERMs (electronic management systems). To ensure the privacy and security of the collected clinical data, only authorized users will be able to access the system and enter, modify, or view the data. All documentation shall be kept for at least 5 years following the conclusion of the experiment, as required by the China Drug Clinical Trial Management Specification.

### Trial quality assurance and control

Quality control and assurance will be handled by CTDMC. A clinical research associate who has been assigned by the sponsor will make regular hospital visits to check that the study is conducted according to plan and that all data are being collected accurately. Before, during, and after the experiment, the investigators will follow SOPs for clinical studies. Inspectors will check case registration forms to ensure accurate and complete information throughout the trial. Researchers will receive training that will standardize their data collection and evaluation practices. To guarantee accurate and trustworthy data, researchers will meticulously document all data on case report forms. Researchers will compare aberrant lab test findings to normal reference ranges. To guarantee that the inferences are valid and based on the original data, we will double-check all of our observations and findings. Relevant data management procedures will be implemented throughout the stages of clinical trials and data analysis. Active measures will be taken to control the dropout rate to within 20%.

### Sample size estimates

According to previous clinical data and our pilot study’s preliminary experiments, 51.9% (42/81, retrospective data) of patients in the untreated group had a good clinical outcome compared with 63.3% (19/30) in the intervention group. The decision to recruit 378 patients (189 in each arm) was based on a power analysis with an alpha of 0.05, a statistical power of 80%, and a 10% loss to follow-up. We decided to enroll 400 patients (200 in each arm). All of the data from the study’s baseline as well as its outcomes were input into the database by a research nurse. The analysis of the data was performed by the research coordinator. The CTDMC checked the data and discussed the findings.

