### Statistical analysis

SPSS 20.0 will be utilized for the analysis of all the data. Measurement data will be expressed as the mean ± SD. After the first half of the patients were recruited, CTDMC evaluated the safety of the trial participants, efficacy, and overall progress of the study and did a masked interim analysis. All patients assigned a random number during the randomization process will be examined using an intention-to-treat analysis. If any measurements in the medical records or outcome measures are found to be incomplete during the statistical analysis, the final data obtained will be considered the final result for use in the statistical analysis.

Two-sample t-tests and odds ratios (OR) with 95% confidence intervals (CI) are provided to identify variations across treatment groups. The criterion for statistical significance will be set at *p* < 0.05. Adjusted odds ratios (aORs) will be calculated using multivariate logistic regression to account for the impact of the treatment facility and any variations in baseline variables for the primary and secondary outcomes. We also did per-protocol and as-treated analyses.

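### The 378 patients (189 per arm) do not follow from 51.9% vs 63.3% at alpha 0.05 and 80% power; 400 patients give about 60% to 64% power, two-sided

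*Protocol article*

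**What the plan says.** Under Sample size estimates, the protocol article reports that "51.9% (42/81, retrospective data) of patients in the untreated group had a good clinical outcome compared with 63.3% (19/30) in the intervention group". These are the only outcome rates it gives. The next sentence describes the sizing as follows: "recruit 378 patients (189 in each arm) was based on a power analysis with an alpha of 0.05, a statistical power of 80" per cent, with a 10% loss to follow-up. Enrolment is then rounded up to 400, or 200 per arm. The section does not give the sidedness, the test or the formula.

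The Abstract gives equal allocation, and Primary outcomes splits the mRS into good (0–3) and poor (4–6), so the calculation is a comparison of two proportions. Under Statistical analysis, significance is p < 0.05 and "odds ratios (OR) with 95% confidence intervals (CI) are provided to identify variations across treatment groups". That section specifies intention-to-treat analysis of all randomized patients, with the last data obtained standing in for incomplete measurements. Follow-up likewise uses the most recent data for patients who cannot be located at 6 months.

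**The concern.** The section prints nearly every input to a standard calculation together with its result, so the result can be checked. An 11-point difference between rates near 50% and 60% normally needs close to 300 patients per arm for 80% power at two-sided 0.05. The plan has 189 per arm before loss.

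At stake is how the primary result will be read. A reader who trusts the stated 80% will think the trial had a one-in-five chance of missing a true effect of the assumed size. If the real chance is nearer 36% to 41%, a non-significant result says much less against the drug than the protocol implies.

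**Working it through.** **Inputs, all from Sample size estimates unless noted**
- Control rate p0: "51.9% (42/81, retrospective data) of patients in the untreated group had a good clinical outcome", so 42/81 = 0.5185 (rounded 0.519).
- Intervention rate p1: "63.3% (19/30) in the intervention group", so 19/30 = 0.6333 (rounded 0.633).
- "a power analysis with an alpha of 0.05" and "a statistical power of 80" per cent; loss 10%.
- Allocation 1:1 (Abstract).
- Sidedness is not stated. Two-sided is assumed because Statistical analysis pairs p < 0.05 with 95% confidence intervals. One-sided is also tried.

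**Step 1. What the plan's figure implies.** 189 × 0.9 = 170.1, and 170/0.9 = 188.9. So 189 per arm is 170 evaluable per arm inflated for 10% loss.

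**Step 2. Evaluable patients needed.** Pooled-variance formula per arm, with p̄ = (p0 + p1)/2:

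n = [z(α)·√(2p̄(1 − p̄)) + z(β)·√(p0(1 − p0) + p1(1 − p1))]² / (p1 − p0)²

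With the exact fractions:
- p1 − p0 = 0.1148 and p̄ = 0.5759
- √(2p̄(1 − p̄)) = √0.4885 = 0.6989
- √(0.2497 + 0.2322) = 0.6942
- n = [(1.960 × 0.6989 + 0.842 × 0.6942)/0.1148]² = (1.954/0.1148)² = 289.7, so 290
- After loss: 290/0.9 = 322.2, so 323 per arm and 646 in total

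With the rounded rates (difference 0.114), n = 294; 294/0.9 = 326.7, so 327 per arm and 654 in total.

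**Step 3. Can another convention give 170?**

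| Method | Evaluable per arm, exact / rounded rates | Per arm after 10% loss |
|---|---|---|
| Two-sided, pooled | 290 / 294 | 323 / 327 |
| Two-sided, unpooled | 287 / 292 | 319 / 325 |
| Two-sided, arcsine | 290 / 294 | 323 / 327 |
| Two-sided, log odds ratio | 293 / 297 | 326 / 330 |
| Two-sided, continuity-corrected | 307 / 312 | 342 / 347 |
| One-sided 0.05, pooled | 229 / 232 | 255 / 258 |
| **Plan** | **170** | **189** |

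Inflating by n × 1.10 instead of n/0.9 changes these figures by only a few patients. The one close match found is a two-sided alpha of 0.20 (169 evaluable, 188 per arm after loss), which conflicts with the stated 0.05.

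**Step 4. Power at the planned sizes.**

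Power = Φ{[(p1 − p0)√n − z(α)·√(2p̄(1 − p̄))] / √(p0(1 − p0) + p1(1 − p1))}

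Example for n = 180, exact fractions, two-sided: (0.1148 × 13.416 − 1.3698)/0.6942 = (1.5404 − 1.3698)/0.6942 = 0.246, and Φ(0.246) = 0.597.

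| Basis | n analysed per arm | Two-sided power (rounded to exact rates) | One-sided power |
|---|---|---|---|
| 378 enrolled, 10% lost | 170 | 56.7% to 57.3% | 68.6% to 69.2% |
| 400 enrolled, 10% lost | 180 | 59.1% to 59.7% | 70.8% to 71.3% |
| 378 enrolled, all analysed | 189 | 61.2% to 61.8% | 72.6% to 73.2% |
| 400 enrolled, all analysed | 200 | 63.7% to 64.3% | 74.7% to 75.3% |

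**Step 5. What 400 patients can detect.** Solving the Step 4 formula for 80% two-sided power from a control rate of 51.9% gives an intervention rate of about 66.4% with 180 per arm (difference 14.5 points) and about 65.7% with 200 per arm (difference 13.8 points). The 170 evaluable behind the plan's 378 correspond to about 66.8%, a difference of 14.9 points; that rate appears nowhere in the article.

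**The case against.** **The right denominator is open.** A reader might say that 189 or 200 patients per arm give only 57% to 60% power. That is not correct as it stands: those figures belong to 170 and 180 evaluable per arm. Statistical analysis and Follow-up keep patients with incomplete outcomes in the analysis through their last available data, so up to 200 per arm may be analysed, with nominal power of about 64%. This stands, and the power has to be quoted with its basis. It does not rescue the 80%.

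**The inputs are partly inferred.** The section does not say outright that 51.9% and 63.3% were the design effect, or that the test was two-sided. The rates are, however, the only ones given, and they directly introduce the power analysis. A one-sided test with all 200 per arm reaches only about 75%. If another effect was used, the section still needs correcting, because it leads the reader to 63.3%.

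**The dropout figures.** A reader might also infer that the 10% loss allowance contradicts Trial quality assurance and control, where "Active measures will be taken to control the dropout rate to within 20" per cent. The documents do not support that. One is a planning value for loss to follow-up and the other a quality-control ceiling on dropout, and both can hold. At most, 20% loss is a sensitivity case: 160 per arm and about 54% to 55% power.

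**This is a condensed article.** Detail left to a fuller document would be no finding. Here the printed inputs and the printed result disagree.

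**Conclusion.** The sample size statement is wrong as written. The stated inputs need about 646 to 654 patients two-sided, against 378 stated and 400 planned. The chance of missing the assumed effect with 400 patients is about 36% (all analysed) to 41% (10% lost and rounded rates), not 20%. That none of the conventions tried reaches 80% does not depend on sidedness, variance formula, rounding of the rates or handling of loss. The exact power does depend on them: it assumes a two-sided 0.05 test of two proportions, the two printed rates as the true rates, and no dilution of the effect by carried-forward values. The finding does not rest on the 20% dropout ceiling.

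**What to change.** Keep 400 patients. In Sample size estimates, delete the claim that 378 patients give 80% power and state sidedness and basis. Suggested wording:

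*400 patients give about 60% power (180 evaluable per arm after 10% loss) to 64% power (all 200 per arm analysed) for 51.9% vs 63.3% at two-sided alpha 0.05, and 80% power for a difference of about 14.5 (180 per arm) or 13.8 (200 per arm) percentage points.*

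If a different effect size was used to reach 378, state that effect and its justification in place of 63.3%. The 54% to 55% power at 20% loss can be added as a sensitivity figure but is not needed.

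The cost is a less favourable stated power, which ethics committees and readers will see. No patients, visits or procedures change.

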### Statistical analysis

SPSS 20.0 will be utilized for the analysis of all the data. Measurement data will be expressed as the mean ± SD. After the first half of the patients were recruited, CTDMC evaluated the safety of the trial participants, efficacy, and overall progress of the study and did a masked interim analysis. All patients assigned a random number during the randomization process will be examined using an intention-to-treat analysis. If any measurements in the medical records or outcome measures are found to be incomplete during the statistical analysis, the final data obtained will be considered the final result for use in the statistical analysis.

Two-sample t-tests and odds ratios (OR) with 95% confidence intervals (CI) are provided to identify variations across treatment groups. The criterion for statistical significance will be set at *p* < 0.05. Adjusted odds ratios (aORs) will be calculated using multivariate logistic regression to account for the impact of the treatment facility and any variations in baseline variables for the primary and secondary outcomes. We also did per-protocol and as-treated analyses.

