## Introduction

Subarachnoid hemorrhage (SAH) is a condition that often occurs in people who have cerebral vascular disease and is hallmarked by increased morbidity and mortality rates and a poor prognosis, particularly in patients who have hypertension. There have been reports indicating that the incidence rate of SAH ranges from 6.2 to 10 cases per 100,000 people in the West (Korja et al., 2016; Mackey et al., 2016; Etminan et al., 2019) and affects approximately 600 000 patients worldwide (Feigin et al., 2009). SAH is associated with a high overall mortality rate that may reach as high as 67% (Nieuwkamp et al., 2009), and only a third of survivors remaining live dependently (van Gijn et al., 2007). Since SAH results in a significant loss of production and resources, it places a considerable cost on society (Zolnourian et al., 2020).

Many previous scholars have attempted to improve outcomes after SAH, and statins (Kirkpatrick et al., 2014; Naraoka et al., 2018), magnesium (Dorhout Mees et al., 2012), and tranexamic acid (Post et al., 2021) are among the medications that have demonstrated superior neuroprotective benefits in basic research; nonetheless, these efforts to enhance outcomes after SAH have primarily been unsuccessful. Although numerous studies have shown that statins or clazosentan may significantly alleviate cerebral vasospasm (CVS), these medications have little impact on the outcomes after a SAH (Macdonald et al., 2011; Chen J. et al., 2020). Despite significant advancements in methods for producing aneurysms, long-term outcomes have not been improved, and there is a lack of medical therapy that is suited for the condition.

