#### Secondary outcomes

The secondary outcome measures were all-cause mortality at 30 days, 6 months Montreal cognitive assessment (Mo-CA), delayed cerebral ischemia, the serum PPAR- γ levels at 1, 3 and 7 days after operation. duration of hospitalization, pulmonary and cardiovascular complications, rebleeding, intensive care unit stay, the incidence of sepsis, the occurrence of hydrocephalus, and treatment modality used to treat the hydrocephalus.

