### Follow-up

The follow-up duration will be 6 months and 12 months beginning from the time when patients were randomized. Patients will be contacted by phone and asked to come back to the hospital for further examinations, which will include conventional CT scans, transcranial Doppler ultrasonography, and neurological scale evaluations. If a patient cannot be located for follow-up, the most recent data evaluated will be used to determine the patient’s values for the 6-month follow-up (Table 1).

**TABLE 1 T1:** Outcome measures and measurement points.

Visit number	Screening period	Follow-up period		
	1	2	3	4
Research arrangement	Screening	In-hospital	30 days	6 months
Informed consent	√			
Selection criteria	√			
Baseline information	√			
General history	√			
Symptoms and physical examination	√			
GCS grading	√			
WFNS grading	√			
Hunt-Hess grading	√			
Conventional brain CT	√	√		
Transcranial Doppler	√	√		
Electrocardiogram	√	√		
Blood sugar	√	√		
Blood NT-proBNP	√	√		
All-cause mortality			√	
mRS score			√	√
Mo-CA			√	√
End point evaluation		√	√	√
Adverse event evaluation		√	√	√
Complications		√	√	√
Intensive care unit stay		√	√	√
Length of hospital		√	√	√
Hospitalization costs		√	√	√

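### Hospital stay, ICU stay and 6-month MoCA fall under a means, t-test and last-value rule that never treats death separately, so if mortality differs these comparisons can favour the arm with more deaths

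*Protocol article*

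**What the plan says.** The Statistical analysis section of the protocol article gives one summary and one test for continuous data: "Measurement data will be expressed as the mean ± SD" and "Two-sample t-tests and odds ratios (OR) with 95% confidence intervals (CI) are provided to identify variations across treatment groups". The adjusted analysis is logistic and so serves binary outcomes only: "Adjusted odds ratios (aORs) will be calculated using multivariate logistic regression to account for the impact of the treatment facility". The analysis set is all randomized patients: "All patients assigned a random number during the randomization process will be examined using an intention-to-treat analysis". For incomplete measurements, "the final data obtained will be considered the final result for use in the statistical analysis". The Follow-up section adds, for the 6-month values, "If a patient cannot be located for follow-up, the most recent data evaluated will be used".

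The Secondary outcomes section lists 30-day all-cause mortality and 6-month MoCA, and also "duration of hospitalization, pulmonary and cardiovascular complications, rebleeding, intensive care unit stay". Table 1 schedules MoCA at 30 days and at 6 months. The Mo-CA section gives a 0–30 scale with cut-offs at 26 and 22, and no value for death. Death counts in only two places: as mRS 6 in the primary outcome, and as 30-day mortality.

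**The concern.** A patient who dies early in hospital has a short stay. Averaged with the rest and compared by t-test, that stay counts in favour of the arm. MoCA has two related problems. Patients who die before any assessment have no score and leave the comparison. Patients who die between day 30 and month 6 have a 30-day score, which the last-value rule can carry into the 6-month comparison as if they were alive.

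Mortality is itself an outcome of this trial, so a difference in deaths is one of the things under study. If there is one, the stay and cognition results can point the opposite way from the mortality result, and the stated p < 0.05 criterion would apply to them as to any other comparison.

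**Working it through.** **What the rules do with a death**

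| Outcome | Patient who dies in hospital before day 30 | Patient who dies between day 30 and 6 months |
|---|---|---|
| Hospital or ICU stay (as a duration) | days to death, taken as a complete stay | observed stay; short if death ended it |
| 6-month MoCA | no score if never assessed, so drops out | 30-day score can stand as the 6-month value |
| mRS (primary) | 6, poor | 6, poor |

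**Figures in the plan.** There is none to reproduce: the article states no mortality rate, stay or MoCA distribution for this trial. Only the 200 per arm comes from the document (Sample size estimates). All other inputs below are assumptions.

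**Assumed inputs for stay.** Survivors: log-normal, mean 20 days, SD 12. In-hospital deaths: exponential time to death, mean m days (so SD m). No treatment effect on survivors' stay. Death proportions are d1 and d2, with d2 the higher.

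**Formulas**
- Difference in mean stay = −(d2 − d1) × (20 − m)
- Variance in an arm = (1 − d) × 12² + d × m² + d(1 − d) × (20 − m)²
- SE = √[(V1 + V2)/200]
- P(deadlier arm significantly shorter) ≈ Φ(|difference|/SE − 1.96)

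**20% vs 30% deaths, m = 7**
- Difference = −0.10 × 13 = −1.30 days
- V1 = 115.2 + 9.8 + 27.04 = 152.04; V2 = 100.8 + 14.7 + 35.49 = 150.99
- SE = √(303.03/200) = 1.231
- P = Φ(1.056 − 1.96) = Φ(−0.904) = 0.18
- With a narrower spread of death times (SD 4 in place of 7): V1 = 145.44, V2 = 141.09, SE = 1.197, P = Φ(1.086 − 1.96) = 0.19

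**All scenarios (exponential death times)**

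| Deaths | Mean day of death | Difference in mean stay | SE | P(falsely favourable), formula | Same, 10,000 simulated trials |
|---|---|---|---|---|---|
| 20% vs 30% | 7 | −1.30 | 1.231 | 0.183 | 0.184 |
| 10% vs 15% | 7 | −0.65 | 1.227 | 0.076 | 0.078 |
| 15% vs 20% | 7 | −0.65 | 1.232 | 0.076 | 0.075 |
| 20% vs 30% | 14 | −0.60 | 1.279 | 0.068 | 0.073 |
| 15% vs 15% | 7 | 0 | 1.230 | 0.025 | 0.025 |

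**Sensitivity.** With less variable stays (gamma; survivors mean 20, SD 8; deaths at mean day 5 to 10, SD 4), the rates are higher: 9–13% for 10% vs 15% deaths and 22–37% across the 10-point differences tried. Equal mortality again gives about 2.5%.

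**MoCA.** Assume mean 22, SD 5, 15% baseline mortality, a correlation of 0.5 to 1 between cognition and survival, and no score for any patient who dies. Then 5 points more deaths raises the mean by 0.18 to 0.37 points, and 10 points more raises it by 0.35 to 0.73. This covers the drop-out of deaths only. The effect of carrying 30-day scores forward depends on how many patients die after day 30, and the article gives nothing to size that.

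**The case against.** **Scope.** The section is a short general statement. It does not assign the t-test to these outcomes by name, and the handling of death could be left to an analysis plan. This stands in part: that the t-test applies to each outcome is an inference from its being the only continuous-data test named. The point is nevertheless more than an omission, because the stated rules together give an answer for a patient who dies, and that answer misleads.

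**Type of outcome.** The Abstract describes the ICU outcome as a requirement for intensive care, which could be binary. MoCA has cut-offs, and adjusted odds ratios are promised for secondary outcomes. This stands, so the ICU point holds only where ICU stay is analysed as a duration. A dichotomised MoCA would still have no category for death.

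**MoCA in survivors only.** A reader might infer that MoCA is simply a survivors' comparison. The last-value rule and the 30-day assessment in Table 1 do not support that; the literal result is a mixture.

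**Size of mortality.** A reader might take the Introduction's "high overall mortality rate that may reach as high as 67" percent as the expected death rate. It is a background upper limit. Sample size estimates gives 51.9% good outcome untreated, which caps death in that series at 48.1%, and the eligibility criteria exclude organ failure and short life expectancy. No mortality difference is projected either.

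**Safeguard.** Mortality is reported alongside. In the simulation, treating in-hospital deaths as the mortality outcome, mortality is also significantly worse in 88% of the falsely favourable trials for 20% vs 30% deaths at mean day 7 (0.1625/0.1842). For 10% vs 15% this falls to 58% (0.0453/0.0779). A reader would often see the conflict, but not always, and the stay p-value itself is not corrected.

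**Conclusion.** The concern holds for secondary outcomes, conditional on mortality differing between arms. The direction for hospital stay follows from the stated rules, provided in-hospital deaths end stays earlier than discharge ends survivors' stays. For MoCA the direction also requires that patients who die would have scored lower.

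The size is illustrative. With stays of mean 20 and SD 12 days and 200 per arm, the falsely favourable rate is about 7–8% for a 5-point excess of deaths or for a 10-point excess of later deaths. It is about 18–20% for a 10-point excess of early deaths, against a nominal 2.5%. Less variable stays raise these figures. With equal mortality there is no inflation.

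A reader might infer that a misleading significant result is the expected outcome for both stay and MoCA. The figures do not support that: in every scenario examined most trials would not show it, and the MoCA shift is under one point. The primary analysis is unaffected because mRS 6 counts as poor.

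**What to change.** **Hospital and ICU stay.** Make the main comparison rank-based (Wilcoxon, stratified by centre) with in-hospital death ranked worst. Alternatively, use days alive and out of hospital or ICU, with death scored 0, over a fixed horizon long enough that few survivors are still in hospital. Under the log-normal assumption about 16% of survivors stay beyond day 30 and would tie with deaths; at day 60 it is about 1%. Report medians and quartiles, with mortality and survivors' stay beside them. State whether the ICU outcome is a duration or a yes/no need.

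**6-month MoCA.** State that a 30-day score is not carried forward for a patient who has died. Rank deaths below the lowest score in the main comparison and show survivors only as supportive.

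**Cost.** Wording only, settled before unblinded analysis. The rank version needs only length of stay and vital status. Days alive and out of hospital also needs readmission dates, which Table 1 does not list. Either measure mixes death with stay or cognition, so the components must be shown.

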#### Mo-CA

Long-term cognitive function is assessed with the Montreal cognitive assessment (MoCA) (Ozdilek and Kenangil, 2014). The MoCA is rated on a scale ranging from 0 to 30 points. The MoCA threshold of 26 points is used to diagnose cognitive impairment and a score of less than 22 is considered to indicate serious cognitive impairment (the optimum threshold score for cognitive domain impairments according to the MoCA) (Wong et al., 2015).

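### The only adjusted model named, logistic regression, does not fit the quantitative secondary outcomes (Mo-CA, serum PPAR-γ, hospital stay)

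*Protocol article*

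**What the plan says.** All wording on adjusted analysis is in the Statistical analysis section of the protocol article. The method is given as "Adjusted odds ratios (aORs) will be calculated using multivariate logistic regression". The adjustment is for treatment facility and "any variations in baseline variables for the primary and secondary outcomes". No second adjusted model is named, and no outcome is exempted.

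For the unadjusted comparison the same section states "Two-sample t-tests and odds ratios (OR) with 95% confidence intervals (CI) are provided to identify variations across treatment groups", and for summaries "Measurement data will be expressed as the mean ± SD".

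The Secondary outcomes section lists, among others, Mo-CA at 6 months, serum PPAR-γ "levels at 1, 3 and 7 days after operation", duration of hospitalization and intensive care unit stay. On Mo-CA, the section of that name says "The MoCA is rated on a scale ranging from 0 to 30 points" and describes two thresholds: "The MoCA threshold of 26 points is used to diagnose cognitive impairment and a score of less than 22" marking serious impairment. Neither threshold is tied to an analysis.

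**The concern.** Ordinary logistic regression needs a two-category outcome. The sentence gives it a scope that includes a score, a repeated laboratory value and a duration. An analyst who follows the text has two courses:

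- cut these outcomes into two groups at a point the plan does not fix, which loses information and leaves the cut open to choice once data are seen; or
- leave them out of the adjusted analysis, so that only a t-test without covariates remains.

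Under the first course, crude and adjusted results for one outcome would also be on different scales: a mean difference beside an odds ratio. Under the second, the stated aim of accounting for centre and baseline is not met for the only cognitive outcome in the trial. At stake are precision and a plan that can be followed as written, for secondary outcomes only.

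**Working it through.** The plan gives no sample size, SD or effect for these outcomes, so there is no figure of its own to reproduce on this point. The check compares outcome types with the model.

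**Step 1. Outcome type against model.** Types are from the Outcome measures sections.

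| Outcome | Scale | Cut fixed for analysis? | Fits binary logistic regression? |
|---|---|---|---|
| mRS | 0–6, split 0–3 / 4–6 | Yes | Yes |
| 30-day mortality, delayed cerebral ischemia, rebleeding, sepsis, hydrocephalus, pulmonary and cardiovascular complications | Event yes/no | Not needed | Yes |
| Mo-CA at 6 months | 0–30 | No; 26 and 22 both described | No |
| Serum PPAR-γ | Continuous, three time points | No; none given | No |
| Duration of hospitalization | Duration | No; none given | No |
| ICU stay | Duration or yes/no | No; none given | Only if yes/no |

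The abstract words the ICU item as a need for intensive care, which would be binary. It is therefore left out of the count: three outcomes clearly do not fit.

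**Step 2. Is the misfit real in practice?** A binary logistic fit to a simulated 0–30 score (200 per arm) was rejected by the software, because the outcome must lie between 0 and 1. A proportional-odds model on the same data ran and gave an odds ratio without any cut, but the article does not name such a model.

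**Step 3. Information kept if an outcome is cut.** For a normal outcome cut at z, the efficiency relative to the uncut comparison is φ(z)² / [Φ(z)(1 − Φ(z))].

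- Median cut, z = 0: 0.3989² / (0.5 × 0.5) = 0.1592 / 0.25 = 0.637.
- One-SD cut, z = 1: 0.2420² / (0.8413 × 0.1587) = 0.0586 / 0.1335 = 0.439.
- Across a range of cuts: 0.58 with 30% of patients below the cut, 0.49 with 20%, 0.34 with 10%.

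To put this in patients, 200 per arm less the plan's 10% loss is 180. A median cut makes these worth about 180 × 0.637 = 115 per arm, and a one-SD cut about 180 × 0.439 = 79. Normality is assumed; Mo-CA is bounded at 30, and the documents give no distribution for it.

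**Step 4. Loss if the outcome is not cut and not adjusted.** Covariates that explain a share R² of the outcome variance reduce the residual variance by the factor 1 − R². The documents give no R² for admission grade, age or centre against any of these outcomes, so this loss cannot be sized. Its direction is clear: the crude t-test is valid under randomisation but less precise whenever R² is above zero.

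**The case against.** The strongest reply is that this is condensed wording. The section pairs means and t-tests with measurement data, and odds ratios with events. On that reading, the adjusted odds ratios cover only outcomes that have an odds ratio, and an article may leave the model for each outcome type to an analysis plan that is not shown. This is a fair guess at the intent. It does not settle the point, for two reasons. The text is not silent: it names a method and gives it a scope that part of the outcome list cannot meet. And the charitable reading leaves the quantitative outcomes with no adjusted analysis in the published text.

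Two stronger readings are tempting and should not be drawn.

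- A reader might infer that Mo-CA, PPAR-γ and hospital stay will have to be dichotomised. Nowhere does the article say so. Its means and t-tests point the other way, and the Mo-CA thresholds are presented as diagnostic.
- A reader might infer that the trial loses the power implied by the 64% and 44% figures. That would follow only if a cut analysis replaced the continuous one, and the t-test is retained.

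The objection also stands on consequence: a crude t-test on a secondary outcome in a randomised trial is valid, and the primary mRS split suits logistic regression.

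**Conclusion.** The point holds as a mismatch between method and outcome, of minor weight. As written, the adjusted analysis of Mo-CA, serum PPAR-γ and duration of hospitalization either depends on cut-offs that are not fixed or does not exist. ICU stay joins them only if it is a duration. If these outcomes were cut, a roughly normal score would keep about 64% of its information at the median and 44% at one SD. If they are not cut, the loss is the precision that centre and baseline adjustment would add, which the documents do not allow to be sized. Neither course biases the crude comparison or touches the primary analysis.

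**What to change.** Replace the sentence on adjusted odds ratios with wording to this effect, before unblinding:

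- Adjusted odds ratios from logistic regression are for binary outcomes only.
- Mo-CA at 6 months: linear regression on treatment, centre, age and admission Hunt-Hess or WFNS grade (one chosen in advance), reporting an adjusted mean difference with 95% CI. The 26 and 22 thresholds are kept as descriptive.
- Serum PPAR-γ: a repeated-measures model over days 1, 3 and 7 with the same covariates.
- Duration of hospitalization: a covariate-adjusted model suited to skewed durations, with a statement of how in-hospital deaths are counted. The same applies to ICU stay if it is a duration; the article should say whether it is.

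Age and Hunt-Hess score are recorded under Procedures, and both grading scales appear in Table 1, so no new data are needed. The Statistical analysis section does not yet name any of them as covariates, so naming them is part of the change. The cost is a few sentences and slightly more analysis work.
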